### Intervention

Prior to randomization, participants will receive behavioral counseling and psychoeducation containing information on nicotine addiction and maintenance and short-term and long-term effects associated with cigarette smoking (about 90 min). Afterwards, smokers will be handed a self-help book (a German copy of *The easy way to stop smoking* by Allen Carr) to aid smoking cessation. Finally, participants will be instructed to record cigarettes smoked throughout the day for the entire study period of 6 weeks. Therefore, our behavioral interventions for smoking cessation include brief behavioral counseling, a self-help book, and the instruction to self-monitor smoking. Taken together, these three interventions constitute the TAU condition. Participants allocated to the experimental condition are then given access to the AAT-training app and are instructed to train at least once per day for 14 consecutive days. Participants perform practice training with the researchers to ensure that the training handling and concepts have been fully understood. To ensure compliance, participants will receive daily reminders via short message service (SMS) to complete the training. After completion of the study (after 6-week follow-up assessment), control condition participants will receive access to the training app.

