### Behavioral and self-report measures

To track daily smoking and possible changes in nicotine consumption, participants are asked to self-monitor their smoking behavior via a cigarette-tracking app, which was specifically designed for the purpose of this study. That is, participants are required to download a native journaling application and are instructed to log cigarettes during or directly after smoking. The data will then be charted on the phone and on the companion website to which it is automatically synchronized. In addition, participants will be asked to estimate their average daily nicotine consumption at pretest, post-training and follow up.

The questionnaire measures will include the Fagerström Test for Nicotine Dependence (FTND) [46] (German version: [47]), the Stages of Change Scale [48] (German version: [49]), the Thoughts About Abstinence Scale [50], attitudes toward smoking based on Swanson et al. [51], the Barratt Impulsiveness Scale (BIS) [52], and the Eysenck Personality Questionnaire - Revised (EPQ-R) [53]. In addition, participants indicate their level of cigarette craving on a 6-point Likert-scale ranging from 0 (“not at all”) to 5 (“very high”). Questionnaire measures will be used to examine group differences at baseline and to assess any changes across the course of the study. At posttest, participants in the experimental condition will be also required to evaluate the app-AAT training and indicate their awareness about the training contingency.

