### Procedure

A time schedule of enrollment, assessment visits, and AAT-app trainings for participants is shown in Fig. 2. During the first laboratory session (baseline; around 180 min) participants give informed consent and take part in a brief behavioral intervention for smoking cessation (TAU). Participants then complete the cognitive bias assessments, the questionnaire measures, and the carbon monoxide breath test. Smokers in the training condition (TAU + training) are given access to the AAT-training app. Participants are instructed to perform the app training on a daily basis for 14 consecutive days. During the second (post-training) and final (6-week follow up) laboratory session, participants complete cognitive bias assessment tasks, questionnaire measures, and the CO breath test. Participants in the experimental condition are asked to evaluate the training and indicate their awareness about training contingencies. Individuals randomized to the control condition will receive access to the training app upon completion of the final follow-up measure. Training data from these participants will not be analyzed.

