To test whether the app training leads to changes in the secondary outcome measures, parametric and non-parametric statistical tests will be administered where appropriate. Close training generalization will be investigated via a 2 (condition: app-training vs control) × 2 (image content: smoking vs positive pictures) × 2 (generalization: trained vs untrained pictures) × 3 (time: baseline, posttest, follow up) mixed-design ANOVA. The 2 (condition) × 3 (time) mixed-design ANOVA will be performed separately for attentional and association biases. Multilevel modeling (MLM) will be used to estimate the growth curve for nicotine consumption as measured with the cigarette training app over time (throughout the entire study period from baseline to follow up). Time will be modeled as a continuous variable. The major advantage of MLM is that it increases power and generalizability by including all individuals regardless of missing data. To examine whether the app-AAT training leads to increased abstinence rates, for each following time point, a separate chi-square test will be carried out with the binary outcome variable (smoking vs nonsmoking) as the parameter of interest. To test the effect of training on other smoking-related variables (i.e., CO, craving, FTND, smoking attitude, motivation to quit), a 2 (condition) × 3 (time) repeated measures multivariate ANOVA (MANOVA) will be conducted. MANOVA with a significant result will be followed up with both univariate tests and discriminant factor analysis. That is, ANOVA will be carried out separately on each of the dependent variables. These analyses will in turn be followed up using contrasts. In addition, discriminant analyses will be applied, which take linear combinations of the dependent variables into account, thereby complementing univariate approaches.

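### The growth-curve model for the cigarette-tracking log (secondary outcome 4) has no pre-training value and, as described, does not use the pretest self-report; adding it and reporting a difference in level would be a cheap gain in precision

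*Protocol article*

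**What the plan says.** **Logging.** The Intervention section makes the log the last step of usual treatment: "Finally, participants will be instructed to record cigarettes smoked throughout the day for the entire study period of 6 weeks". Self-monitoring is itself part of that treatment: "our behavioral interventions for smoking cessation include brief behavioral counseling, a self-help book, and the instruction to self-monitor smoking". The next step is the training: "Participants allocated to the experimental condition are then given access to the AAT-training app". The Procedure section puts these steps in one visit, the first laboratory session, in which "participants give informed consent and take part in a brief behavioral intervention for smoking cessation (TAU"), complete the assessments and, in the training arm, receive the app. No logging run-in is described.

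**Model.** Data preparation and planned analyses specifies a multilevel model with this aim: "estimate the growth curve for nicotine consumption as measured with the cigarette training app over time (throughout the entire study period from baseline to follow". On the time variable it adds: "Time will be modeled as a continuous variable". It gives no functional form, time origin, covariate or treatment contrast. The sentence calls the source the training app. Outcome measures and Behavioral and self-report measures make clear that the tracking app is meant.

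**Pre-training value that does exist.** Behavioral and self-report measures says: "In addition, participants will be asked to estimate their average daily nicotine consumption at pretest, post-training and follow up". For the primary outcomes, the analysis section controls for baseline consumption when it compares arms at post-test and follow-up. It does not repeat this for the tracked series.

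**The concern.** The first logged day already follows app access in the training arm, so the log cannot serve as its own baseline. Two consequences follow.

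- **Level.** A comparison of logged level between arms carries the full between-person variation in smoking unless another pre-training measure is brought in. The trial collects such a measure, and the model description does not use it.
- **Slope.** A growth-curve comparison is commonly read from the condition-by-time term. Training is confined to the first 14 of about 42 days. If its effect builds quickly and then holds, the arms differ in level from early on but little in rate of change. A slope-only reading would then understate a lasting effect.

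At stake is the trial's only daily smoking record.

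**Working it through.** **1. The plan's own figure.** The Sample size section gives 74 participants in total for the primary outcomes. With d = 0.30 (f = 0.15), 3 time points and r = 0.5, the noncentrality is λ = N·f²·m/(1 − r) = 74 × 0.0225 × 3 / 0.5 = 9.99, which gives power 0.806. Then 74 / 0.75 = 98.7, or 99, rounded up to 100. The figure reproduces. No figure is stated for the tracked endpoint, so what follows rests on assumptions.

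**2. Share of an early, lasting effect that a straight-line slope shows.** Assume an effect that rises linearly to its full size E by day k and then stays constant, with daily logs on days 1 to 42. The slope is b = Σ(t − 21.5)·e(t) / Σ(t − 21.5)², where the denominator is 42 × (42² − 1) / 12 = 6170.5. The change over the period is 41·b.

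For k = 3 with the ramp starting from zero on day 0, the effect falls short of E by 2/3 on day 1 and by 1/3 on day 2. The numerator is 20.5 × 2/3 + 19.5 × 1/3 = 20.17, and 41 × 20.17 / 6170.5 = 0.134. With zero effect on day 1 instead, the numerator is 20.5 + 19.5 × 1/2 = 30.25, and the share is 0.201. The other rows use the same steps:

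| Effect complete by | Ramp from day 0 | Ramp from day 1 | Slope change if E = −3 cigarettes/day (ramp from day 0) |
|---|---|---|---|
| day 3 | 13% | 20% | −0.40 |
| day 5 | 26% | 32% | −0.78 |
| day 7 | 38% | 44% | −1.13 |
| day 14 | 71% | 77% | −2.14 |

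The part that the slope does not show is not lost from the model. With a knot at day 14, k = 3, E = −3 and the ramp from day 0, the fitted difference is −2.35 on day 1. It changes by −0.77 to day 14, giving −3.12 there. The effect is divided between intercept and slope.

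**3. Precision of a level contrast.** In units of the between-person SD with 50 per arm, SE = √(2/50) = 0.20. Adjusting for a covariate with correlation r multiplies this by √(1 − r²):

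- r = 0.5: factor 0.866, SE 0.173, a fall of 13%.
- r = 0.7: factor 0.714, SE 0.143, a fall of 29%.

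Power for a 0.30 SD difference in level is 32% unadjusted, 41% at r = 0.5 and 56% at r = 0.7. With 37 per arm after attrition it is 25%, 32% and 44%.

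**4. Simulation.** Assumed: 50 per arm, subject SD 1, daily residual SD 0.6, random-slope SD 0.5 over 42 days, correlation 0.7 with the pretest report, 3,000 runs. Rejection rates at the 5% level:

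| True effect | Slope | Intercept | Mean level | Mean level, adjusted |
|---|---|---|---|---|
| None | 5% | 4% | 5% | 5% |
| 0.30 SD, immediate and sustained | 5% | 29% | 28% | 47% |
| 0.30 SD, building linearly to day 42 | 71% | 4% | 11% | 16% |

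The null row shows that chance imbalance does not inflate the error rate. The other two rows show that neither contrast serves both patterns.

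**The case against.** The strongest reply is that the article never says the effect is the slope alone or that time is linear. A growth curve has an intercept and a slope, and condition can enter either. Covariates, form and contrast of a secondary model are details that an article may leave to a fuller document. This stands: the slope figures are conditional on a reading that the text permits but does not state.

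A reader might infer that the model cannot tell an early training effect from chance imbalance. The documents do not support that. Allocation is random and 1:1, so an intercept or level contrast is a valid test whose standard error already covers chance differences. Starting usual treatment and logging together affects both arms alike.

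A reader might also take the phrase about the curve running from baseline as a misstatement. It only describes the study period, and baseline is the article's name for the first session.

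Early onset is an assumption too. The Background suggests that repeated sessions are needed for stable change, and for an effect complete only at day 14 the slope shows most of it.

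Finally, the stakes are limited. Secondary outcomes are declared explorative, and self-reported cigarettes per day, a primary outcome, has a pretest value and baseline control. A fast, lasting effect would therefore also be tested there.

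What remains is that a pre-training value is collected, is used for the primary comparisons, and is not carried into the description of this model.

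**Conclusion.** The point holds as a matter of precision and of which contrast is read, not of bias. The tracked series has no pre-training value, and the model as described makes no use of the pretest self-report. Under a slope-only, straight-line reading, 13–20% of an effect complete by day 3 would appear in the slope, 38–44% by day 7 and 71–77% by day 14. Adjustment would cut the standard error of the level contrast by about 13% to 29%.

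These figures assume a ramp-and-hold effect, a straight line over days 1 to 42, and a correlation of 0.5 to 0.7 between pretest report and logged consumption. The documents give no correlation for that pair; the r = 0.5 in the Sample size section concerns the primary repeated measures. It would go too far to conclude that a real effect will be reported as none, or that the trial's conclusions are undermined. The endpoint is secondary and exploratory, and this is an optional, cheap improvement.

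**What to change.** In Data preparation and planned analyses:

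- Enter pretest self-reported cigarettes per day as a covariate in the multilevel model.
- Report the baseline-adjusted difference between arms in model-estimated daily cigarettes at post-training and at follow-up. Keep the growth-rate contrast beside it, since that contrast is the better test of an effect that builds slowly.
- State the time origin and the form of time, because model-estimated levels also depend on them.
- Name the tracking app, not the training app, as the data source.

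The cost is wording only. No new data are needed, and the article states that the trial had not started at submission. One small downside is that the covariate is a recalled average, on a slightly different scale from logged counts. As a covariate it need not share their scale, but a weaker correlation would reduce the gain.

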### Outcome measures

We focus on two primary outcome measures: (1) changes in smoking-related approach biases with regard to smoking stimuli presented during training (measured in milliseconds) and (2) reductions in self-reported daily cigarette smoking (measured in number of smoked cigarettes per day). Primary time points include post-training and follow-up assessments. Secondary outcome measures are (1) changes in smoking-related approach biases with regard to untrained pictures (close generalization), (2) changes in approach biases for positive pictures, (3) changes in other cognitive biases as measured by the visual dot-probe task and the Implicit Association Task (IAT) (broad generalization), (4) self-monitored smoking behavior using a cigarette tracking app, (5) biochemically verified abstinence rates defined as point prevalence with a 7-day window prior to the assessment point, (6) expired CO, and (7) other self-reported smoking behavior.

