### Sample size

A priori power analyses were conducted using G*Power 3.1 (open-source software [34]). Previous research investigating the effectiveness of CBM training identified a small-to-moderate effect size [21, 35]. We conducted a power analysis for a 2 × 3 mixed design ANOVA to detect a small-to-moderate effect (Cohen’s *d* = 0.30, α = 0.05) for the interaction between experimental condition and time for each primary outcome and time point. Power of 0.80 and *r* = 0.5 for correlation between the repeated measures was assumed. Results indicated that 74 participants in total would be needed. Due to an expected attrition rate of approximately 25% at follow up (defined as dropout at any time point after completing the baseline assessment), we decided to include 100 participants, that is 50 per condition.

We would like to stress that we performed power calculations for primary outcomes exclusively. With regard to secondary outcome measures, we emphasize that the study is explorative, meaning that any significant findings on these outcome variables should be interpreted with caution until tested in further confirmatory RCTs.

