### Randomization and blinding

Participants will be randomly assigned to the experimental or the control group with a 1:1 allocation ratio, according to an externally constructed randomization plan. To do so, a computer-generated randomization schedule will be employed by means of a computerized random number generator using IBM SPSS Statistics 24. Permuted block randomization will be used to ensure that study groups of approximately the same size are generated. Block size will be set to 50 participants. No other stratification will be used. The study coordinator will perform randomization. Due to the study design, it is not possible to blind participants. However, to avoid bias in the outcome assessment, research assistants concerned with data collection and/or preparation will be blind to the allocation of the participants.

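### Expired CO, the only continuous biochemical measure of smoking, gets a test of its own only after a significant five-variable MANOVA

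*Protocol article*

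**What the plan says.** The Outcome measures section names self-reported cigarettes per day as the smoking primary. Its list of secondary outcomes ends with "6) expired CO, and (7) other self-reported smoking behavior", so CO stands apart from the self-report scales. Item (5) of the same list is biochemically verified 7-day point-prevalence abstinence. The Biochemical verification section describes expired CO, at all three visits, and no other biochemical measurement.

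On blinding, the protocol says: "Due to the study design, it is not possible to blind participants". Research assistants who collect or prepare data are blind to allocation.

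In Data preparation and planned analyses, CO appears in one place: "To test the effect of training on other smoking-related variables (i.e., CO, craving, FTND, smoking attitude, motivation to quit", followed by a single 2 × 3 repeated-measures MANOVA. The next step is conditional: "MANOVA with a significant result will be followed up with both univariate tests and discriminant factor analysis". The univariate step is a separate ANOVA on each dependent variable, then contrasts. Other secondary outcomes in that section carry no such condition. Attentional and association biases each get their own 2 × 3 ANOVA, the cigarette-tracking record gets a multilevel model, and abstinence gets a chi-square test at each later time point.

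**The concern.** Participants know their arm, and the training arm is told what the training is meant to change. A difference in self-reported cigarettes per day could therefore partly reflect reporting. Blinded research assistants do not remove that, because the participant supplies the number. The tracking-app record is also logged by the participant. Continuous CO is the one planned measure that could support or question a reduction among people who still smoke.

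Under the stated rule, whether CO is tested depends on a joint test shared with four self-report scales. If those scales do not respond, they add degrees of freedom without adding signal, and a real CO effect may never reach its own test. The protocol gives no reason for placing CO behind this step while leaving cognitive biases outside it.

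**Working it through.** **Inputs from the Sample size section.** "Cohen’s *d* = 0.30, α = 0.05"; "Power of 0.80 and *r* = 0.5 for correlation between the repeated measures was assumed"; "Results indicated that 74 participants in total would be needed"; "expected attrition rate of approximately 25% at follow up"; 100 randomised, 50 per arm. The MANOVA has five outcomes at three times, which gives 5 × 2 = 10 interaction contrasts.

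**Step 1: the plan's own figure.** Read d = 0.30 as f = d/2 = 0.15. For the condition × time interaction with m = 3 times, λ = N·m·f²/(1 − r) = N × 3 × 0.0225/0.5 = 0.135N, on 2 and 2(N − 2) df. Power is 0.795 at N = 72 and 0.806 at N = 74, so 74 reproduces as the smallest even total. Then 74/0.75 = 98.7, or 99; the plan uses 100. At N = 100 the power is 0.914.

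**Step 2: the same effect placed on CO.** This is an assumption, since the protocol states no effect for CO. For a difference of δ SD present at both later visits, λ = (N/4)(2/3)δ²/(1 − r) = Nδ²/3. Setting this to 0.135N gives δ² = 0.405, so δ = 0.636 SD.

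**Step 3: power of the joint test, effect on CO only, outcomes uncorrelated.** Hotelling's T² on 10 contrasts has 10 and N − 11 df, with λ unchanged.
- N = 74: λ = 9.99, power 0.47, against 0.81 for CO alone (0.80 if CO's two change scores are tested by T²).
- N = 100: λ = 13.5, power 0.65, against 0.91.
- For a smaller effect of δ = 0.5 SD, again with T² on the two change scores for CO alone: 0.29 against 0.58 at N = 74, and 0.41 against 0.72 at N = 100.

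**Step 4: other assumptions.** Simulation used 4,000 runs per scenario, the doubly multivariate test, and all measures scored in the same direction. *Gated* is the probability that both the MANOVA and CO's own ANOVA are significant.

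| Assumed effects | Correlation between outcomes | N = 74: CO alone | N = 74: gated | N = 100: CO alone | N = 100: gated |
|---|---|---|---|---|---|
| CO only | 0 | 0.811 | 0.466 | 0.915 | 0.634 |
| CO only | 0.3 | 0.809 | 0.544 | 0.910 | 0.743 |
| CO only | 0.5 | 0.803 | 0.666 | 0.915 | 0.853 |
| CO full, other four half | 0 | 0.805 | 0.717 | 0.914 | 0.888 |
| CO full, other four half | 0.3 | 0.811 | 0.506 | 0.915 | 0.677 |
| CO full, other four half | 0.5 | 0.809 | 0.439 | 0.926 | 0.641 |
| All five equal | 0 | 0.797 | 0.797 | 0.922 | 0.922 |
| All five equal | 0.3 | 0.801 | 0.747 | 0.914 | 0.903 |
| All five equal | 0.5 | 0.814 | 0.667 | 0.910 | 0.856 |

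The averaged Wilks form of the MANOVA is slightly kinder: 0.50 to 0.80 gated at N = 74, and 0.68 to 0.92 at N = 100 over these scenarios.

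**Step 5: what the condition buys.** With no effect on any outcome (N = 74, correlation 0.3), CO's own ANOVA is significant in 4.8% of runs. CO passes both steps in 1.1%.

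**The case against.** The case for leaving the plan alone has real weight, and much of it stands.

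- **CO is not the only objective outcome.** A reader might infer that the MANOVA condition removes every biochemical comparison. It does not: verified abstinence has its own unconditional chi-square tests. What remains is that abstinent-or-not says nothing about a reduction among continuing smokers, which is what the cigarettes-per-day primary measures.
- **Testing is conditional, reporting is not.** A reader might infer that CO results would go unreported after a non-significant MANOVA. The article says only which tests follow a significant one. Descriptive tables may well be left to the full protocol or analysis plan.
- **CO does not depend on the other scales.** It can make the MANOVA significant unaided, at lower power, and once the MANOVA is significant CO gets its own ANOVA. So a result driven by the self-report scales would still lead to a CO test.
- **Near-halving is a worst case.** It needs N = 74 and either an effect confined to CO with uncorrelated outcomes, or weaker effects on correlated scales. Multiple imputation is planned for ITT, so the analysis set is nominally 100, where the worst relative loss is about 31%.
- **Secondary outcomes are declared exploratory and were not powered.** An omnibus test over several such outcomes is a recognised guard against false positives, as Step 5 shows. But the same section tests other exploratory outcomes without it, and the protocol already asks for caution with any significant secondary result.

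**Conclusion.** The point holds in a limited form. The plan lists continuous CO as its own secondary outcome, yet conditions its only specific test on a five-variable MANOVA shared with four self-report scales. This is a stated rule, not a detail left out of a condensed article.

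At N = 74 the cost runs from nothing (all five respond equally, uncorrelated), through about 15 points (all respond equally, correlation 0.5), to a fall from about 80% to 44–47%. At N = 100 the worst case is a fall from 91% to about 63–65%. These figures assume that the protocol's powered effect applies to CO and is sustained at both later visits, that r = 0.5 over time, that each construct has one score, and that correlations between outcomes lie between 0 and 0.5. The protocol fixes none of these for CO, so the range matters more than any single figure.

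The primary analyses are unaffected. The issue is how well a self-reported reduction can be corroborated.

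**What to change.** Take expired CO out of the MANOVA. Prespecify its own analysis, either baseline-adjusted comparisons at post-training and follow-up or a 2 × 3 condition × time model, not conditional on the MANOVA. Report the estimate with a 95% CI beside self-reported cigarettes per day. Keep the MANOVA for craving, FTND, smoking attitude and motivation to quit.

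This changes analysis wording only. CO is already scheduled at every visit, and the Trial status section says the trial had not started at submission. The downside is one more exploratory test without omnibus protection: its false-positive rate returns to the nominal 5%. Label it exploratory, in line with what the Sample size section says about secondary outcomes.
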